## **15.0**

### **QUALITY CONTROL AND QUALITY ASSURANCE**

To ensure the quality and reliability of the data gathered and the ethical conduct of this study, a Study Operations Manual (SOM) will be developed. The SOM includes requirements for reporting and documenting deviations.

Regular monitoring will be performed according to ICH-GCP as indicated in Section 17.3.

An independent audit of the study may be performed by the Sponsor or their designee.

By signing the protocol, the Principal Investigators agree to facilitate study related monitoring, audits, IRB/IEC review and regulatory inspection(s) and direct access to source documents. Such information will be treated as strictly confidential and under no circumstances be made publicly available.

## **16.0 DATA AND BIOLOGICAL MATERIAL**

All data and biological material collected through the study shall be managed in accordance with the Clinical Trial Agreement (CTA). Distribution and use of these data will be conducted by agreement of all parties.

The computerized raw data generated will be held by the DCC on behalf of the Sponsor. The CRC will also hold the final data files and tables generated for the purpose of analysis. The Principal Investigator or designees will have access to the clinical database with appropriate blinding.

## **17.0 ADMINISTRATIVE STRUCTURE**

The Principal Investigator will be responsible for all aspects of the study at the CRC.

### **17.1 Protocol Safety Review Team**

The Protocol Safety Review Team (PSRT) will be formed to monitor the clinical safety data. During the vaccination phase of the trial, the PSRT will review clinical safety data on a weekly basis. An *ad hoc* PSRT review meeting will occur if any of the members of the PSRT requests a special review to discuss a specific safety issue or as specified in the Study Operations Manual.

The PSRT will consist of the IAVI Medical Monitor(s) and PI or designee from each clinical team. An IAVI Medical Monitor will be the PSRT Chair. *Ex officio* members will include the IAVI CMO, IAVI Medical Safety Monitor and representatives from Profectus Biosciences Inc. and Ichor Medical Systems, Inc.

Additional PSRT participants may include the following, as needed:

- Co-investigators and CRC senior clinical research nursing staff
- Laboratory directors
- Data management, study statistician and regulatory staff

The Terms of Reference for PSRT and procedures to be followed are detailed in the SOM.

### **17.2 Safety Review Board**

The Safety Review Board (SRB) will oversee the progress of the study. The SRB will consist of independent clinicians/scientists/statisticians who are not involved in the study. Investigators

responsible for the clinical care of volunteers or representative of the Sponsor may not be a member of the SRB.

However, the SRB may invite the Principal Investigator(s) or designee and a Sponsor representative to an open session of the meeting to provide information on study conduct, present data or to respond to questions.

All safety data will be reviewed by an independent Safety Review Board (SRB) once the first 15 volunteers randomized across all groups have reached the M 2.5 and M 6.5 time points.

### **17.2.1 Content of Interim Safety Review**

The SRB will be asked to review the following data:

- Summary of reactogenicity (i.e., solicited adverse events)
- All clinical adverse events judged by the Principal Investigator or designee to be possibly, probably or definitely related to the Investigational Product
- All laboratory adverse events confirmed on retest and judged by the Principal Investigator or designee to be possibly, probably, or definitely related to Investigational Product and/or clinically significant
- All SAEs

An unblinded presentation of all above-noted events will also be available for the SRB for their review if required by any member of the SRB.

### **17.3 Criteria for Pausing the Study**

Enrolment and vaccinations will be stopped and a safety review conducted by the SRB for any of the following criteria:

- one subject experiences an SAE that is probably or definitely related to the investigational vaccine(s), or two or more subjects experience similar SAEs which are possibly related to the investigational vaccine(s);
- there is a subject death assessed as possibly, probably or definitely related to the investigational vaccine(s)
- one subject experiences injection site ulceration, sterile abscess or necrosis associated with vaccine administration; or
- one subject experiences a severe allergic reaction, such as laryngospasm, bronchospasm or anaphylaxis, associated with vaccine administration.

The Sponsor will request a review by the SRB, or the SRB chair if other SRB members cannot be convened, to be held within 2 business days of the Sponsor learning of the event. The individual volunteer(s)/or study may be unblinded at the discretion of the SRB.

Following this review, the SRB will make a recommendation regarding the continuation or suspension of the vaccinations or the trial and communicate this decision immediately to the Sponsor. The Sponsor then will inform the Principal Investigators without delay.

Additional *ad hoc* review may be specifically requested by the Sponsor, the Principal Investigator(s) or by the SRB.

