| EVALUATION FOR INTER-CURRENT HIV INFECTION:       | 
Volunteers will be tested for HIV according to the Schedule of Procedures. Test results will be interpreted according to a pre-determined diagnostic algorithm. Should one or more serological HIV test(s) post-vaccination be positive, a nucleic-acid-based HIV test will be performed to distinguish a true HIV infection acquired through exposure in the community from HIV seropositivity due to the vaccine-induced antibody response. HIV testing at additional time points may be performed upon request of the volunteer and principal investigator or designee as medical or social circumstances warrant.
 
To maintain blinding of study staff with direct contact with the volunteers, HIV test results will be reported to the clinical team as “HIV-uninfected” or as “HIV-infected” (ONLY once intercurrent HIV infection is confirmed).
                                                                                                                                                                                                                                                  |
| SAFETY MONITORING AND STATISTICAL CONSIDERATIONS: | 
All clinical trial data collected, identified only by a volunteer identification number, will be entered into a database.
 
Safety will be continually monitored by the Investigators, the Sponsor’s Medical Monitor and a Protocol Safety Review Team (PSRT); detailed stopping criteria are pre-defined.
 
All safety data will be reviewed by an independent Safety Review Board (SRB) once the first 15 volunteers randomized across all groups have reached the M 2.5 and M 6.5 time points.
 
Ad-hoc safety review may be specifically requested by the Sponsor, Profectus, Ichor, the Principal Investigators, Ethics Committees, Regulatory Authorities, or by the SRB.
 
At the end of the study, a full analysis will be prepared according to a pre-specified statistical analysis plan. In addition, there may also be interim reviews of blinded data. All clinical and routine laboratory data will be included in the safety analysis. Immunogenicity analysis will be performed according to a predefined analysis plan for all volunteers who received vaccine or placebo.
 |

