## 12. DISCONTINUATION OF VACCINATIONS AND/OR WITHDRAWAL FROM STUDY

### 12.1 Discontinuation of Vaccinations

Any discontinuation or planned discontinuation from further vaccinations will be discussed with the Sponsor. Volunteers will be discontinued from further vaccination for any of the following reasons:

1. Pregnancy
2. Intercurrent HIV Infection
3. Use of systemic corticosteroids, immunosuppressive, antiviral, anticancer, anti-tuberculosis or other medications considered significant by the investigator. Note: Volunteers requiring chronic corticosteroids (> 2 weeks) or long term therapy will not receive any further vaccinations.
4. A disease or condition or an adverse event that may develop, regardless of relationship to the Investigational Product, if the Principal Investigator or designee is of the opinion that further study vaccinations will jeopardize the safety of the volunteer
5. Anaphylaxis, bronchospasm, laryngeal oedema, convulsions or encephalopathy following study vaccinations
6. Life-threatening adverse event following study vaccination unless not related to the Investigational Product and fully resolved

7. Any immediate hypersensitivity reaction judged to be related to the Investigational Product, if the Principal Investigator or designee is of the opinion that further study vaccinations will jeopardize the safety of the volunteer
8. Volunteer's request to discontinue further vaccination

The following are parameters that require resolution and/or review of clinical history by the Principal Investigator or designee and consultation with the Medical Monitor, prior to continuation of study vaccination(s):

1. Any of the following abnormal laboratory parameters that are known at the time of vaccination:

*Haematology*

- Haemoglobin  $\leq 9.0$  g/dL **or**  $\leq 5.55$  mmol/L
- Absolute Neutrophil Count (ANC):  $\leq 1000/\text{mm}^3$  **or**  $\leq 1.0 \times 10^9/\text{L}$
- Absolute Lymphocyte Count (ALC):  $\leq 500/\text{mm}^3$  **or**  $\leq 0.5 \times 10^9/\text{L}$
- Platelets:  $\leq 90,000 \geq 550,000/\text{mm}^3$  **or**  $\leq 90 \times 10^9 \geq 550 \times 10^9/\text{L}$

*Chemistry*

- Creatinine:  $>1.4 \times \text{ULN}$
- AST:  $\geq 2.6 \times \text{ULN}$
- ALT:  $\geq 2.6 \times \text{ULN}$

2. Receipt of inactivated/killed/subunit vaccines (non-HIV) or immunoglobulin within the previous 14 days or planned receipt within 14 days after vaccination with Investigational Product

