| Fever (nonaxillary)                                                                                                                                                 | 37.7 – 38.6°C                                                                         | 38.7 – 39.3°C                                                                                                     | 39.4 – 40.5°C                                                                                            | > 40.5°C                                                                                                                                                                        |
| Pain (indicate body site)
DO NOT use for pain due to injection (See Injection Site Reactions: Injection site pain)
See also Headache, Arthralgia, and Myalgia | Pain causing no or minimal interference with usual social & functional activities     | Pain causing greater than minimal interference with usual social & functional activities                          | Pain causing inability to perform usual social & functional activities                                   | Disabling pain causing inability to perform basic self-care functions OR Hospitalization (other than emergency room visit) indicated                                            |
| Unintentional weight loss                                                                                                                                           | NA                                                                                    | 5 – 9% loss in body weight from baseline                                                                          | 10 – 19% loss in body weight from baseline                                                               | ≥ 20% loss in body weight from baseline OR Aggressive intervention indicated [e.g., tube feeding or total parenteral nutrition (TPN)]                                           |

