| Injection site reaction (localized)                                                         |                                                                                                                                                    |                                                                                                                                             |                                                                                                                                                                                                         |                                                                                                                                                                        |
| Adult > 15 years                                                                  | Erythema OR Induration of 5x5 cm – 9x9 cm (or 25 cm  – 81cm  )                                                             | Erythema OR Induration OR Edema > 9 cm any diameter (or > 81 cm  )                                                              | Ulceration OR Secondary infection OR Phlebitis OR Sterile abscess OR Drainage                                                                                                                           | Necrosis (involving dermis and deeper tissue)                                                                                                                          |
| Pediatric ≤ 15 years                                                                 | Erythema OR Induration OR Edema present but ≤ 2.5 cm diameter                                                                                      | Erythema OR Induration OR Edema > 2.5 cm diameter but < 50% surface area of the extremity segment (e.g., upper arm/thigh)                   | Erythema OR Induration OR Edema involving ≥ 50% surface area of the extremity segment (e.g., upper arm/thigh) OR Ulceration OR Secondary infection OR Phlebitis OR Sterile abscess OR Drainage          | Necrosis (involving dermis and deeper tissue)                                                                                                                          |

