| Neuromuscular weakness
(including myopathy & neuropathy)                                                              | Asymptomatic with decreased strength on exam OR Minimal muscle weakness causing no or minimal interference with usual social & functional activities | Muscle weakness causing greater than minimal interference with usual social & functional activities                                                  | Muscle weakness causing inability to perform usual social & functional activities                                                                  | Disabling muscle weakness causing inability to perform basic self-care functions OR Respiratory muscle weakness impairing ventilation                                                                            |
| Neurosensory alteration
(including paresthesia and painful neuropathy)                                                | Asymptomatic with sensory alteration on exam or minimal paresthesia causing no or minimal interference with usual social & functional activities     | Sensory alteration or paresthesia causing greater than minimal interference with usual social & functional activities                                | Sensory alteration or paresthesia causing inability to perform usual social & functional activities                                                | Disabling sensory alteration or paresthesia causing inability to perform basic self-care functions                                                                                                               |
| Seizure: ( new onset ) –
Adult ≥ 18 years
See also Seizure:
(known pre-existing seizure disorder) | NA                                                                                                                                                   | 1 seizure                                                                                                                                            | 2 – 4 seizures                                                                                                                                     | Seizures of any kind which are prolonged, repetitive (e.g., status epilepticus), or difficult to control (e.g., refractory epilepsy)                                                                             |

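### Section 17.3 has no automatic study pause for a vaccine-related Grade 4 event that is not an SAE, or for a non-serious convulsion or encephalopathy associated with vaccination

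*Protocol*

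**What the plan says.** Section 17.3 opens with "Enrolment and vaccinations will be stopped and a safety review conducted by the SRB for any of the following criteria" and gives four criteria:

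1. one subject with a probably or definitely related SAE, or two or more subjects with similar possibly related SAEs;
2. a death at least possibly related;
3. one subject with injection-site ulceration, sterile abscess or necrosis associated with vaccine administration;
4. one subject with a severe allergic reaction associated with vaccine administration.

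The sponsor then asks for an SRB review, to be held within 2 business days of learning of the event.

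Section 12.1 item 5 ends an individual's vaccinations for "Anaphylaxis, bronchospasm, laryngeal oedema, convulsions or encephalopathy following study vaccinations". Item 6 does the same for a life-threatening event, unless it is unrelated and fully resolved.

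Other oversight is as follows. Under section 17.1, during the vaccination phase "the PSRT will review clinical safety data on a weekly basis", and the team meets ad hoc if a member "requests a special review to discuss a specific safety issue or as specified in the Study Operations Manual". The Synopsis adds that an ad hoc "safety review may be specifically requested by the Sponsor, Profectus, Ichor, the Principal Investigators, Ethics Committees, Regulatory Authorities, or by the SRB". Section 17.2 schedules SRB reviews when the first 15 volunteers reach M2.5 and M6.5.

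**The concern.** Criteria 3 and 4 show that the sponsor accepts single-event triggers that do not require seriousness, but only for local tissue injury and allergy. In Appendix C the adult Grade 3 injection-site reaction reads "Ulceration OR Secondary infection OR Phlebitis OR Sterile abscess OR Drainage". So one Grade 3 sterile abscess stops enrolment and dosing, while a related fever or ALT value in the highest grade does not unless it also becomes an SAE.

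Similarly, 12.1 item 5 puts convulsions and encephalopathy beside anaphylaxis and bronchospasm for the individual, but 17.3 carries only the allergic reactions to study level.

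At stake is whether the independent board is certain to see such an event promptly. Section 3.2 reports no safety data yet for HIV-MAG, and section 3.3 says no clinical study has yet been conducted of HIV-MAG with GENEVAX IL-12.

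**Working it through.** **Step 1. Each event against the automatic triggers.**

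| Event | Appendix C grade | SAE under 10.4 by itself? | 17.3 trigger |
|---|---|---|---|
| Sterile abscess | 3 | not required | yes, one subject |
| Fever above 40.5 °C | 4, by value | no | none |
| ALT above 10 x ULN | 4, by value | no | none |
| One new-onset seizure | 2 | not necessarily | none |
| 2–4 new-onset seizures | 3 | not necessarily | none |

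Appendix C states that severity and seriousness are different things, so Grade 4 does not imply SAE. A Grade 4 rule alone would miss a single seizure, so convulsion needs its own line.

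**Step 2. Do the other safeguards guarantee SRB review?**
- The Protocol Safety Review Team consists of sponsor Medical Monitors and site investigators, with company representatives ex officio. It is not independent; the SRB is (17.2).
- Ad hoc SRB review happens on request.
- The stagger in 7.8 covers the first four volunteers.
- Medical Monitor consultation under 12.1 for ALT at or above 2.6 x ULN applies to values known at vaccination. In Groups 1–3 (Appendix A) chemistry is drawn at screening, then at D28 and D56, which are the dosing days. A rise after dose 1 may not be known when dose 2 is given.

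None of these is an automatic study-level step.

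**Step 3. How often would a Grade 4 trigger fire?** The protocol gives no event rates, so the per-volunteer rates p are assumed. The chance that at least one volunteer has the event is 1 − (1 − p)^n. The chance of at least two is 1 − (1 − p)^n − n·p·(1 − p)^(n−1).

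*Low background rates, all 75 volunteers (the blind is kept, so placebo recipients count):*

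| p | one event suffices | two events needed |
|---|---|---|
| 0.1% | 1 − 0.999^75 = 7.2% | 0.3% |
| 0.25% | 17.1% | 1.5% |
| 0.5% | 1 − 0.995^75 = 31.3% | 5.5% |

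*Higher rates in the 60 vaccine recipients:*

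| p | one event suffices | two events needed |
|---|---|---|
| 1% | 45.3% | 12.1% |
| 2% | 70.2% | 33.8% |
| 5% | 95.4% | 80.8% |

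*Only one regimen of 12 affected:* 46%, 72% and 93% at rates of 5%, 10% and 20% if one event suffices; 12%, 34% and 73% if two are needed.

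A rule that pauses on one probably or definitely related event, or two similar possibly related ones, falls between the two columns, depending on how events are attributed. Under the present text the chance is zero at every rate.

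**Step 4. Exposure if the safety team acts at its weekly review.** Assume even accrual of 75 volunteers over 3 months (84–91 days). At the busiest point, 75/84 = 0.893 volunteers a day enter, and 60% of them (Groups 1–3, 45 of 75) have two further prime doses: 0.893 × (1 + 0.6 × 2) = 1.96 administrations a day, or 1.81 at 91 days. One week is then 12.7–13.7 administrations.

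**The case against.** The strongest reply is that this is a choice and not an error. Individual and study-level rules need not match, and naming the local injuries that electroporated DNA might cause is not a severity ranking. That stands: a reader might infer that 17.3 contradicts 12.1 or Appendix C, and it does not. The comparison with the sterile abscess shows only that a non-serious event can be a trigger.

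The gap is also narrow. The general Grade 4 definition and the SAE definition overlap on intervention to prevent permanent impairment, and SAEs also cover life-threatening events and hospitalisation. Most clinical Grade 4 events and most encephalopathies would therefore be SAEs, and any prior seizure is an exclusion criterion. What remains is mainly fever, laboratory values and a non-serious convulsion. Section 3.5 gives some reassurance on the Ad35 component: B001 reported 165 non-serious events, 2 severe, 58 moderate and 105 mild (2 + 58 + 105 = 165), so none was Grade 4. B001 says nothing about HIV-MAG with IL-12.

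A reader might also infer that such events would go unseen until the first scheduled SRB review, and count every dose given before it as exposure. The documents do not support that: review is weekly, and its members are among those who can call the SRB. The Study Operations Manual, not shown, may add triggers.

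None of this supplies an automatic independent review.

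**Conclusion.** The point holds as a cheap improvement. Section 17.3 fixes an explicit list which, followed exactly, never pauses the trial for a related non-serious Grade 4 event or for a non-serious convulsion or encephalopathy. Prompt independent review of these depends on someone asking for it. The residual risk is modest: if the safety team acts at its next weekly meeting, about 13–14 administrations could fall in between at peak accrual, under the even-accrual assumption. The trigger probabilities rest on assumed rates and show how often a rule would fire; they do not measure harm. The conclusion also assumes that the Study Operations Manual does not already set these triggers.

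**What to change.** Add two criteria to 17.3 under the existing 2-business-day SRB process:

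- (a) one subject with a probably or definitely related Grade 4 event, or two or more subjects with similar possibly related Grade 4 events, laboratory values confirmed on retest;
- (b) one subject with a convulsion or encephalopathy associated with vaccine administration, whatever its grade.

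Part (a) copies the attribution rule of the SAE criterion. Pausing on a single possibly related Grade 4 value would rank it above a single possibly related non-fatal SAE, which does not pause the trial. Part (b) uses the association wording of the injection-site and allergic criteria, so an unrelated late convulsion does not count. A count trigger for Grade 3 events is not needed. If the Study Operations Manual already holds such triggers, state them in 17.3.

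The cost is amendment wording and an occasional extra pause, sometimes for a placebo recipient. For part (a), at an assumed rate of 0.1% per volunteer, at most about 7% of trials would pause, and at 0.5% at most about 31%; both are lower when events are judged only possibly related. Part (b) would add to this, and no rate is available for it. Two business days are 2–4 calendar days, so at 1.81–1.96 administrations a day a pause defers about 4–8 at peak accrual (1.81 × 2 = 3.6; 1.96 × 4 = 7.9). That is not a ceiling: 17.3 sets when the review is held but not when dosing restarts.
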